### Study design

The study starts with a standard care visit in which all patient characteristics are collected. During this visit, blood will be collected to measure total IgE (tIgE), specific IgE (sIgE) to inhalation allergens, and eosinophils to map the asthma profile of the patient. After that, all patients undergo spirometry with reversibility. If there is no reversibility, the patient will ask to participate in the study.

In a separate appointment, the BPT test (standard care) and FeNO-test (extra) will be done, and the diagnostic burden will be measured (Visual Analogue Scale (VAS)) after each test. After the study visit, the patient will receive the results of the FeNO-test and the BPT and will be treated.

if they are diagnosed with asthma or get extra investigations if there is no asthma (standard care 2). After 3 months, patients will be medically controlled by the pulmonary physician for evaluating treatments and quality of life with the Asthma Control Questionnaire (ACQ) and Asthma Quality of Life (AQLQ) (standard consult 3, digital consult), and 2 additional questionnaires will be administered. The study program and diagnostic results are shown in Table 1; Fig. 1.

**Table 1 Tab1:** Study program

Standard care 1.	• Consult pulmonary physician • Blood testing • Spirometry
**Study visit 1**	• BPT (standard care) • Informed consent • FeNO-test (extra) • Questionnaires (VAS) (2, extra)
Standard care 2.	• Results of the FeNO-test and BPT • Diagnosis • Possible treatment • Possible additional investigations
Standard care 3.	• ACQ, AQLQ after 3 months of treatment (digital consult)

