### Statistical analysis

Patient- and study characteristics will be reported in percentages, means, and standard deviation. The cost reduction of incorporating the FeNO-test in the new diagnostic algorithm will be established by the number of theoretically avoided BPT, theoretically avoided days of absenteeism caused by the BPT, and extra FeNO measurements. The decrease in burden will be studied by calculating differences in VAS-score and AQLQ-score after the BPT and FeNO-test with an independent T-test. The mean delta ACQ after 3 months of treatment in the patients with asthma and without asthma will be determined and also compared with an independent T-test. The accuracy of the FeNO-test will be calculated by comparing the FeNO-test outcomes to the (gold standard) BPTs outcomes in terms of sensitivity and specificity. A p-value of 0.05 will be considered statistically significant. The post-hoc analysis will be performed for subgroups of the patients; smokers and obese patients.

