## Ethics and dissemination

The local medical ethics committee; Medical Research Ethics Committees United (MEC-U), approved the proposed study (registration number R23.005).

This study has a low burden for the participating patients because the new diagnostic work-up does not differ much from the standard diagnostic work-up. Only the FeNO-test (5 min), a very simple and low-burden lung function test is extra. The worst side effect of the FeNO-test is light-headedness. The blood sampling is the same as in routine diagnostics for asthma. The patient could get a hematoma and sometimes patients have a vasovagal collapse. Also, the BPT test (70 min) is routine diagnostics for asthma. Side effects are dyspnea symptoms/ hyperresponsivity. The patients’ questionnaires will take 5 min after each diagnostic test and after 3 months. We expect no risk for the study patients.

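### The plan compares a mean change in ACQ at 3 months, but the printed schedule names the ACQ only at 3 months, so no change score can be formed from it

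*Protocol article*

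**What the plan says.** The Statistical analysis section of the protocol article states: "The mean delta ACQ after 3 months of treatment in the patients with asthma and without asthma will be determined". The sentence goes on to say that the result is determined "and also compared with an independent T-test".

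The Study design section gives the schedule twice. The text says: "After 3 months, patients will be medically controlled by the pulmonary physician for evaluating treatments and quality of life with the Asthma Control Questionnaire (ACQ"). The same sentence also names the AQLQ. In Table 1 the ACQ appears in one row, standard care 3: "ACQ, AQLQ after 3 months of treatment (digital consult"). The questionnaire entry for study visit 1 is "Questionnaires (VAS) (2, extra"). For the first visit, the text says only this about baseline data: "The study starts with a standard care visit in which all patient characteristics are collected".

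The Ethics and dissemination section gives the questionnaire burden without naming instruments: "The patients’ questionnaires will take 5 min after each diagnostic test and after 3 months".

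The Outcomes section says that asthma control will be measured by questionnaire in the different groups. It defines neither a baseline nor a change.

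**The concern.** A delta is a difference between two measurements on the same patient. The analysis names the delta, but the schedule supplies only its end point. If sites follow Table 1, the analyst will have 3-month ACQ scores and nothing to subtract from them. The likely outcome is that 3-month levels are compared and reported under the name of a change. A level mixes how severe the patient was at the start with what happened afterwards.

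The same sentence raises a lesser question of interpretation. It speaks of 3 months of treatment in patients with and without asthma, whereas the Study design text ties treatment to an asthma diagnosis and gives the other patients further investigations. Even with a baseline, the t-test would compare groups that differ in diagnosis and, largely, in treatment.

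A pre-treatment ACQ cannot be collected once treatment has begun, so the gap grows with each patient enrolled under the printed schedule.

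**Working it through.** No figure in the article is attached to the ACQ analysis, so the check sets the sections side by side.

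**1. What the analysis needs.** For patient i, delta_i = ACQ_i(3 months) − ACQ_i(before treatment). Two values per patient are required.

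**2. What the schedule supplies (Study design, Table 1).**

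| Visit | Content named | ACQ? |
|---|---|---|
| Standard care 1 | Consult, blood testing, spirometry; the text adds unspecified patient characteristics | Not named |
| Study visit 1 | BPT, consent, FeNO-test, two VAS questionnaires | Not named |
| Standard care 2 | Results, diagnosis, possible treatment, possible further investigations | Not named |
| Standard care 3 | ACQ and AQLQ at 3 months | Yes |

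The ACQ is named at one of four visits, which gives one value per patient. The delta in step 1 has no subtrahend.

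**3. Could delta mean the difference between groups?** This does not fit the sentence. The delta is first determined in the patients with and without asthma, and the t-test is then an additional comparison of those results. It reads as a mean within-patient change in each group.

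**4. Could the two additional questionnaires in the Study design text be a baseline ACQ?** That sentence places them at the 3-month contact. If they are instead the two extra VAS forms of Table 1, they belong to study visit 1 and are not the ACQ. Neither reading gives a baseline.

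**5. What is lost if 3-month levels are used instead.** Write A for patients with asthma and N for patients without. For group means,

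level(A) − level(N) = [baseline(A) − baseline(N)] + [change(A) − change(N)].

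The difference in levels equals the difference in changes only if the two groups have the same mean baseline ACQ. Nothing in the article says that they do, and the groups are formed by diagnosis.

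**6. Does the defect reach the sample size or the main aims?** The stated sample size uses prevalence 0.39, sensitivity 0.60 and specificity 0.85:

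- avoidable share = 0.39 × 0.60 + 0.61 × 0.15 = 0.3255
- n = 1.96² × 0.3255 × 0.6745 / 0.075² = 149.9, so 150, as stated (reading the CI of 0.15 as a full width)
- at 49.2%: 1.96² × 0.492 × 0.508 / 0.075² = 170.7, so 171, as stated

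The ACQ enters none of these. Avoided BPTs, costs, VAS burden, and sensitivity and specificity also use no ACQ value.

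**The case against.** The strongest defence is that the printed schedule may not be complete. Fig. 1 is cited with Table 1 as showing the study program. It is not shown in the text reviewed, and its legend lists the ACQ without a time point. The first visit collects unspecified patient characteristics. The Statistical analysis section also refers to an AQLQ score after the BPT and the FeNO-test, which Table 1 does not list at study visit 1, so Table 1 may be condensed. This stands as a limit: the documents do not prove that no baseline ACQ is collected. It does not remove the mismatch. The article prints a visit-by-visit schedule, names the ACQ in it at one time only, and then plans an analysis that this schedule cannot feed. An analysis plan can define a delta but cannot supply a measurement that was not taken.

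A reader might infer four stronger things that the documents do not support:

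- **That all 171 patients will certainly lack a baseline.** This holds only under the schedule as printed, for the reasons above.
- **That the Ethics section independently confirms the gap.** It names no instrument. It is compatible with the gap but does not establish it.
- **That the safeguard for false-positive FeNO results fails.** The Discussion describes a clinical check of individual patients after 3 months, in future practice without a routine BPT. It does not mention the ACQ or a group mean change. In this study every participant is planned to have both tests, so false positives are identified against the BPT.
- **That the comparison should be BPT-positive against BPT-negative patients among those with FeNO ≥ 50 ppb.** On the article's inputs these groups would be about 171 × 0.39 × 0.60 = 40 and 171 × 0.61 × 0.15 = 16. Because treatment follows diagnosis, this contrast might again compare treated with untreated patients. It is a preference, not a correction.

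The article also does not say that patients without asthma stay untreated, only that they receive further investigations. And it never claims that the asthma versus no-asthma comparison tests the FeNO pathway. What remains is a caution about how to describe the result.

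**Conclusion.** The point holds in a limited form. As printed, the article plans a within-patient change in ACQ and schedules one ACQ per patient, at 3 months. No pre-treatment ACQ is named in any section, so the planned delta cannot be formed under that schedule. This rests on two assumptions: that Fig. 1 does not show an earlier ACQ, and that the unspecified patient characteristics at the first visit do not include one. If either fails, Table 1 and the Study design text still need to be brought into line with it.

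The whole of this one analysis is affected, but nothing beyond it. Asthma control is a secondary outcome, and the main aims and the sample size do not depend on it. Should-fix.

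**What to change.** 1. Add the ACQ to Table 1 and the Study design text before treatment starts, at standard care 1 or study visit 1. Study visit 1 is where Table 1 places informed consent. If it is used, give the ACQ before the two tests, since the Discussion notes that BPT symptoms can persist. If a baseline ACQ is already collected, state where.
2. Replace the t-test on the delta by an analysis of the 3-month ACQ adjusted for the baseline ACQ, and report the baseline means of both groups.
3. For patients enrolled without a baseline, report the 3-month ACQ level only and do not call it a delta.
4. State that the comparison of patients with and without asthma is descriptive and is not an estimate of treatment effect, because treatment is tied to the diagnosis. Baseline adjustment does not change this.

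If no baseline can be added, the minimum is to remove the word delta and describe the analysis as a comparison of 3-month scores.

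The cost is a small amendment and a few minutes per patient. Taking the 5 minutes that the Ethics section allows for each questionnaire occasion, this is at most 171 × 5 = 855 minutes, about 14 hours of patient time over the whole study. The sample size does not change.

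### The analysis compares a change in ACQ, but the printed schedule names the ACQ only once, at 3 months, and no text shown names a score before treatment

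*Protocol article*

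**What the plan says.** The Statistical analysis section plans this for asthma control: "The mean delta ACQ after 3 months of treatment in the patients with asthma and without asthma will be determined". The sentence ends by saying that this quantity "will be determined and also compared with an independent T-test".

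The Study design section places the ACQ at one time. Its prose reads: "After 3 months, patients will be medically controlled by the pulmonary physician for evaluating treatments and quality of life with the Asthma Control Questionnaire (ACQ". Table 1 agrees and lists, under Standard care 3, "ACQ, AQLQ after 3 months of treatment (digital consult". At Study visit 1, the only questionnaire entry in Table 1 is "Questionnaires (VAS) (2, extra". The Outcomes section names asthma control as something to be measured by questionnaire in the groups, without a time point.

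Two other places bear on timing. On the first visit, Study design says: "The study starts with a standard care visit in which all patient characteristics are collected". In the account of patient burden under Ethics and dissemination, the "questionnaires will take 5 min after each diagnostic test and after 3 months".

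**The concern.** The analysis section and the schedule do not fit together. The first needs two ACQ scores per patient, and the second names one. This is not a detail that an article can leave to an analysis plan. The article prints both the schedule and the analysis, and an analysis plan cannot create a score that was never collected.

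What is at stake is the article's only stated analysis of asthma control. A single score at 3 months shows how well controlled patients are at that time. It cannot show whether control changed after diagnosis and treatment. The two groups are formed by diagnosis, so they may have differed in ACQ from the start, and a difference at 3 months alone cannot be read as a difference in change. The loss also grows with time: each patient who starts treatment without a recorded ACQ has no obtainable baseline afterwards.

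**Working it through.** The plan gives no figure for the ACQ, so the check is a count of scheduled scores.

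**What the analysis needs.** For patient i, delta = ACQ at 3 months − ACQ before treatment. That is one score on each side of the start of treatment.

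**What the schedule names (Table 1).**

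| Contact | Timing | Questionnaires named | ACQ |
|---|---|---|---|
| Standard care 1 | before treatment | none (consult, blood, spirometry) | 0 |
| Study visit 1 | before treatment | two VAS | 0 |
| Standard care 2 | results, diagnosis, possible treatment | none | 0 |
| Standard care 3 | 3 months | ACQ, AQLQ | 1 |

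Scores named before the 3-month contact: 0 + 0 + 0 = 0. Scores named at 3 months: 1. The prose of Study design gives the same count.

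**Other text that might supply a baseline.**
- Outcomes: no time point for asthma control.
- First visit: patient characteristics are collected, but the ACQ is not named among them, and Table 1 itemises that visit without it.
- Ethics and dissemination: questionnaires follow each diagnostic test and recur at 3 months. The forms are not named, so this neither supplies a baseline ACQ nor excludes one.
- Fig. 1: Study design cites it together with Table 1 as showing the programme, and its legend spells out ACQ. The figure is not shown, so a baseline there cannot be ruled out.

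**Could delta mean something that needs no baseline?** It could be read as the difference between the groups at 3 months. The sentence works against this. It determines a mean delta in the patients with and without asthma, and then also compares it. Delta is the quantity compared, not the comparison.

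**How many patients.** With the intended 171 patients and the prevalence of 0.39 from the Sample size calculation, the comparison would involve about 171 × 0.39 = 66.7, or 67, patients with asthma and 171 × 0.61 = 104.3, or 104, without. On the printed schedule, neither group has a baseline.

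**What does not depend on it.** The plan's sample size can be reproduced without the ACQ. The avoidable share is 0.39 × 0.60 + 0.61 × 0.15 = 0.3255. With a total interval width of 0.15 (half-width 0.075), n = 1.96² × 0.3255 × 0.6745 / 0.075² = 149.9, or 150, as stated. At the upper share of 0.492, n = 1.96² × 0.492 × 0.508 / 0.075² = 170.7, or 171, as stated.

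**The case against.** The strongest reply is that Table 1 may not be the full schedule. Fig. 1 is cited beside it and is not shown. The article condenses a fuller protocol. There is also a sign that the table omits forms: the Statistical analysis section plans to compare AQLQ scores after the provocation test and the FeNO-test, yet Table 1 lists the AQLQ only at 3 months. That may mean that study-visit questionnaires are missing from the table, or it may be a second inconsistency. The ACQ is also not marked as extra in Table 1, so it may be a routine instrument, and a pre-treatment score may be on file.

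Much of this stands. A reader might infer that no baseline exists for any patient and that the outcome is already lost. The documents do not support that. They show that no baseline is named in the text, which is weaker. What the reply does not remove is the conflict in the printed text. If Fig. 1 holds a baseline ACQ, then Table 1 and the prose are incomplete and still need correction.

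It is also fair to say that the stated aims are avoided provocation tests, cost-effectiveness and burden. The ACQ receives one sentence in the analysis section and does not appear in the abstract's methods. This limits how serious the point can be.

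**Conclusion.** The point holds in a conditional form. As printed, the schedule provides 0 ACQ scores before treatment and 1 at 3 months, and the planned change needs one of each. Unless Fig. 1 or routine care supplies a baseline, the change cannot be computed for any of the 171 patients, and it could not be repaired at analysis. This should be fixed. Confidence is medium, because Fig. 1 is not shown.

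Two stronger readings are not supported. One is that the gap undermines the study's main conclusions. It does not: the sample size, the count of avoided tests, the costs and the accuracy analysis make no use of the ACQ. The other is that the t-test on change should give way to a model of the 3-month score adjusted for baseline. Patients with and without asthma are not randomised groups and may differ at baseline. A change-score comparison and an adjusted comparison then answer different questions, and the choice between them is open. Either one needs the baseline that the text does not schedule.

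**What to change.** Add the ACQ to Study visit 1, in Table 1 and in the prose of Study design, to be completed after consent, before the provocation test and the FeNO-test, and before any treatment. In Statistical analysis, define delta ACQ as the 3-month score minus that score. If Fig. 1 already shows a baseline ACQ, correct Table 1 and the prose to match it.

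For patients who have no baseline, report the 3-month score only, do not call it a delta, and state how many patients this concerns.

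An editorial side note: the prose says that at 3 months "2 additional questionnaires will be administered" without naming them, while the two extra forms in Table 1 are the VAS at Study visit 1. Name them or align the two places.

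The cost is one short questionnaire at a visit that already takes place, a one-line change to the table and one sentence in the analysis section. The downside is a few extra minutes for patients, and still no delta for those already past that visit without a recorded score.

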### Patient and public involvement

The Dutch Advisory Council of the patient representation was involved in the development of this study protocol and will be permanently involved during the study. A patient information session will be organized twice a year, in which this research project is evaluated. Patient Reported Experience Measures (PREMs) Patient Reported Outcome Measures (PROMs) will be used in this evaluation.

## Discussion

This study is the first care evaluation study that aims to calculate the cost-reduction and reduction in burdensome for the patient if the FeNO-test is implemented in the diagnostic work-up for asthma.

The FeNO-test is not (not yet) included in the asthma diagnostic flowchart of the GINA guideline, because the FeNO-test cannot replace the BPT (gold standard) entirely [15].

However, the UK National Institute for Health and Care Excellence (NICE) asthma guidelines recommend the use of the FeNO-test in the diagnostic asthma work-up [10]. Also, the ERS task force recommends the measurement of FeNO as part of the diagnostic work-up of children aged 5–16 years and adults with suspected asthma [2, 3].

A FeNO-test cut-off value above 40–50 ppb yields a specificity between 0.75 and 0.95 and a sensitivity between 0.19 and 0.81 for a diagnosis of asthma [2]. The high variability observed across the studies reflected differences in patient inclusion criteria in demographics, such as smoking and atopy status, or concurrent inhaled corticosteroid treatment during assessment [16, 17]. High FeNO levels may also be observed in other diseases such as eosinophilic chronic bronchitis and allergic rhinitis. The FeNO-test can be used to rule in a diagnosis of asthma with confidence, however, the poor sensitivity does not allow asthma to be ruled out [15].

This is the first study that investigates the value of the FeNO-test (cut off ≥ 50 ppb) as add-on test, intending to determine the impact of the FeNO-based strategy, in terms of the number of avoided BPTs, cost-effectiveness, and reduced burden on the patient and health care.

The total economic burden of asthma is high due to the prevalence of the disease with direct costs e.g. emergency visits, physician visits, and diagnostic tests, and indirect costs e.g. work and school absence [18]. Therefore, it is important to reduce costs. Preventing BPTs by adding the FeNO-test as an extra diagnostic tool in de asthma diagnostic work-up will substantially decrease asthma costs for health care by speeding up the diagnostic process. Significant costs can be avoided by saving the challenge test in the expected 50% of the patients as they will have a FeNO- test result with a value of ≥ 50 ppb. These will be the patients with Type-2 high asthma (allergic/eosinophilic asthma). This type of asthma is the most common type of asthma: about 50-70% of people with asthma have an underlying type 2 inflammation [9].

Moreover, the BPT is unpleasant for the patient and not without side effects. BPT can cause symptoms such as wheezing, pharyngeal itching, cough, or chest tightness with sometimes persistence of symptoms for several days. This is not the case with the FeNO-test and these side effects can therefore be avoided in a significant number of patients. Three studies in a meta-analysis of a Dutch Cochrane review showed no difference in the quality of life between the group with a FeNO-test and the control group (no diagnostic intervention) (MD = 0.02; 95% CI -0.10 to 0.14), which demonstrates that the de FeNO-test is a low-burden test for the patient [6]. The FeNO-test is considered low-burden, fast, and ensures cost reduction compared to the BPT [6].

A limited capacity is also available in most lung function labs in the Netherlands for BPTs. Since lung function technicians are scarce in the Netherlands, patients face long waiting lists. This is very patient-unfriendly and can lead to temporary undertreatment of the patients.

The limitation of the new diagnostic approach is that a small group of patients is at risk of being misdiagnosed with a false-positive FeNO-test in the future if the BPT is no longer performed for the asthma diagnostic control as in this study context. The size of this group depends on the accuracy of the FeNO-test. The assumption is a specificity of 90% (10% false positive FeNO-test) [2]. This is a sketch based on the mean percentages from the literature. The patients will be checked whether they have an effect on the treatment after 3 months and if there are doubts about the treatment effect then to perform the BPT.

In conclusion, this is the first study that investigates the value of the FeNO-test (cut off ≥ 50 ppb) as an add-on test in asthma diagnostics. The hypothesis is that the BPT will not be necessary for about 50% of the patients. This will substantially reduce asthma costs and burden for the patient and healthcare professionals. The ultimate goal is to adjust the GINA - and National asthma guidelines with the new diagnostic work-up. The current asthma diagnostic work-up is unsustainable in the future, because of the increase in the number of asthma patients, increase in healthcare costs, and increasing lung function waiting lists.

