### Outcomes

The reduction in the number of provocation tests will be calculated by adding up the number of theoretically saved provocation tests. The decrease in direct and indirect costs will be calculated by adding up the costs of the number of provocation tests and the absence days, which were not necessary afterward, minus the extra costs of the FeNO measurement. The reduction in patient burden will be assessed with questionnaires. Asthma control and quality of life will be measured in the different groups using questionnaires. The accuracy of the FeNO test will be calculated by comparing the FeNO test results with the gold standard results of the challenge test.

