### Sample size calculation

The sample size calculation is based on the prevalence, sensitivity, and specificity based on the percentages in the literature. A prevalence of asthma is taken at 0.39, the sensitivity of the FeNO-test at 0.6 (mean of 0.5–0.7 (for patients with type-2 high asthma)), and the specificity at 0.85 (mean of 0.75 to 0.95). This leads to 32.55% avoidable BPTs and an associated sample size is 150 patients. When we take the margins into account and accept a CI of 0.15, this leads to percentages avoidable BPT of 16.9–49.2% and an associated sample size of 96–171 patients. We have the intention to include 171 patients. The sample size calculation with all margins is shown (Supplementary S1).

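### The avoided-BPT count and the cost saving are gross of the 3-month BPT that the Discussion describes for doubtful treatment effect, so both are upper bounds

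*Protocol article*

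**What the plan says.** All references are to the protocol article.

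- **Outcomes.** The reduction in provocation tests "will be calculated by adding up the number of theoretically saved provocation tests". The cost reduction is the cost of the BPTs and absence days that turn out not to be needed, "minus the extra costs of the FeNO measurement". No other deduction is named.
- **Statistical analysis.** The cost reduction has the same three ingredients: avoided BPTs, avoided absenteeism and extra FeNO measurements.
- **Sample size calculation.** Prevalence is 0.39, FeNO sensitivity 0.6 and specificity 0.85. "This leads to 32.55% avoidable BPTs and an associated sample size is 150 patients".
- **Study design and Table 1.** Every participant has both the BPT and the FeNO-test at study visit 1. Results are given before treatment starts. Patients diagnosed with asthma are treated, and those without asthma go on to further investigation. ACQ and AQLQ follow at 3 months.
- **Discussion.** A paragraph on a limitation of the new approach says that some patients could be misdiagnosed through a false-positive FeNO-test once the up-front BPT is dropped. It closes with a check of treatment effect after 3 months and, "if there are doubts about the treatment effect then to perform the BPT".

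**The concern.** In the FeNO-based route, a patient with FeNO ≥ 50 ppb skips the BPT at the start. If that patient has a BPT at 3 months because the treatment effect is in doubt, the test has been postponed, not avoided. The test, its cost and any absence days are then incurred after all.

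The Discussion relies on this later BPT to limit the harm of misdiagnosis, while the outcome and cost definitions value the route as if it never took place. Any error runs in one direction only, because a net count cannot exceed the gross count. The number of avoided BPTs and the cost saving are what the authors want to bring to the guidelines, so a reader should be able to see whether the figures describe the route with its follow-up rule or without it.

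**Working it through.** **1. Where the 3-month BPT belongs.** All participants have a BPT at study visit 1, and the Discussion sentence sits in a paragraph about a future in which that BPT is no longer done. The conditional BPT is therefore part of the future route.

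**2. The plan's own figure.** With prevalence 0.39, sensitivity 0.60 and specificity 0.85 (Sample size calculation):

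- true positives: 0.39 × 0.60 = 0.2340
- false positives: 0.61 × 0.15 = 0.0915
- sum: 0.3255, the stated 32.55%

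The sample size also reproduces, reading the CI of 0.15 as the full width of a 95% interval for one proportion: n = 1.96² × 0.3255 × 0.6745 / 0.075² = 149.9, so 150. The planning figure is thus the gross share of FeNO-positive patients, each counted as one avoided BPT. Of 171 patients, 55.7 would be FeNO-positive: 40.0 true and 15.6 false positives.

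**3. Net share.** Let f and g be the shares of true and false positives who have a BPT at 3 months. The documents give neither, so the values below are assumptions.

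Net share = 0.2340 × (1 − f) + 0.0915 × (1 − g)

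| f | g | Net share | Net avoided of 171 | Deferred BPTs | Gross exceeds net by |
|---|---|---|---|---|---|
| 0 | 0 | 32.55% | 55.7 | 0 | 0% |
| 0.1 | 0 | 30.2% | 51.7 | 4.0 | 8% |
| 0 | 1 | 23.4% | 40.0 | 15.6 | 39% |
| 0.2 | 1 | 18.7% | 32.0 | 23.6 | 74% |

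For example, the last row is 0.2340 × 0.8 + 0 = 0.1872, and 0.3255 / 0.1872 = 1.74.

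**4. Cost.** Let A be the gross avoided BPTs, D the deferred BPTs, b the cost of a BPT, d the cost of the absence days per BPT, e the cost of a FeNO-test and N the number of patients.

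- as written: A(b + d) − Ne
- net: (A − D)(b + d) − Ne
- overstatement: D(b + d)

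The FeNO cost stays fixed. If the saving as written is positive, its relative loss is therefore larger than D/A, which is 7%, 28% and 42% in the last three rows of the table. The article gives no unit costs, so this cannot be put in money.

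**5. Sample size.** The same precision formula at the net shares gives 144, 123 and 104 patients, all below 171.

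**The case against.** The case for leaving the plan as it is has several parts.

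- **The rule is a single Discussion sentence.** The Abstract defines the new work-up only as FeNO placed between spirometry and BPT, and the Discussion calls its misdiagnosis estimate a sketch. This stands as a limit. A reader might infer that the article makes the rule a formal part of the work-up or claims safety on the strength of it, but the article presents misdiagnosis as a limitation. It also names no primary outcome, so the avoided-BPT count should not be called one.
- **The rule may concern false positives only.** The sentence closes a paragraph about them. A reader might infer that correctly diagnosed patients with a poor response are certainly covered. The trigger, doubt about treatment effect, allows that reading, and without a BPT the two groups cannot be told apart, but it remains an inference. The 23.4% scenario does not need it.
- **The wording may already be net.** The count is labelled theoretical, and the cost sentence could be read with hindsight. However, no deduction for a later BPT is stated, and the planning figure is demonstrably gross.
- **The article is condensed.** Scenario analyses may be left to a fuller document. But the article does state the outcome, the cost terms and the follow-up rule, and these do not fit together.
- **The size is unknown.** This stands. All three net scenarios also lie within the article's own planning range of 16.9–49.2%.

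**Conclusion.** The point holds as a mismatch between the Discussion and the outcome and cost definitions. The count and the saving, as defined, are upper bounds for a FeNO-based route that includes the 3-month BPT. The direction is certain, given that at least some patients would be retested. The size is not: 30.2%, 23.4% or 18.7% against 32.55% are scenarios on the planning inputs, not estimates.

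Two stronger readings are not supported. The sample size is not undermined. Nor can the study observe directly how often the rule would be triggered, for example by recording doubt at the 3-month review. That doubt would be formed with the BPT result already known, and BPT-negative patients may not have been treated at all.

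**What to change.** 1. Reconcile the Discussion with Outcomes and Statistical analysis by stating whether the evaluated route includes the 3-month BPT. Which clinical rule applies is for the investigators to settle.
2. Label the gross count *BPTs initially omitted*.
3. Report next to it a net count and a net cost that subtract deferred BPTs and their absence days over a stated range of retest shares. Set the range separately for BPT-positive and BPT-negative patients with FeNO ≥ 50 ppb.
4. For treated BPT-positive patients, let the 3-month ACQ data already being collected inform the range, with the caveat that physicians and patients know the BPT result. For untreated BPT-negative patients, show the range from none to all retested.

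This needs no new procedure or visit and no change in sample size. It costs a little more analysis and a somewhat smaller stated saving.
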